#### Sample size calculation

A two-tailed power calculation for 70 % power and *P* = 0·05 was performed using G * Power software, for a *t* test with linear regression (two independent groups) and an effect size of d = 0·6, based on results from similar neuroimaging studies^(42)^, determining that thirty-four participants per group (AN/healthy) would be sufficient. To account for potential dropouts or unforeseen issues, thirty-six participants will be recruited for each group to ensure robust statistical analysis.

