While these observations indicate that neuronal networks in the brain integrate metabolic and psychological aspects of eating differently in AN, it is unclear how this perturbed metabo–psychological integration contributes to AN development and maintenance^(52)^. No previous report has, to our knowledge, revealed in what way the connection between psychology and metabolism mediates core symptoms of AN; that is, no one has distinguished either what neuronal networks respond to the psychological *contra* metabolic aspects of eating a meal or how those networks integrate their information to affect patients’ food intake, distorted body image and fear of weight gain. The identification of the mechanisms that drive AN is also hampered by the current tendency of published studies to focus on adults rather than adolescents although adolescence is the time when most patients develop AN. The ISRCTN and Clinicaltrials.gov registers (as of October 2025) record neither any recent nor ongoing trials anywhere in the world aimed to answer these questions. No current clinical trials of AN comprehensively speak to metabo–psychological mechanisms of change.

The primary objective of the Networks Integrating Anxiety and Metabolism in Anorexia Nervosa (NAMA) trial is to distinguish between the neural response to eating caloric and non-caloric meals and how this differs between newly diagnosed adolescents with AN and matched healthy controls. Secondary objectives examine the effects of caloric and non-caloric food intake on endocrine, circulatory, psychological and behavioural responses in patients with AN and healthy controls. By integrating behavioural, psychological and physiological aspects of food intake with brain network analyses, the NAMA trial will investigate what drives AN. We hypothesise that calorie-dependent changes in network activity will differ between AN patients and healthy controls and that calorie intake will predict aggravated AN-related symptoms in patients: lower food intake, worse fear of gaining weight and increased feeling of being overweight.

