## Experimental methods

### Design

The study is designed as a single-centre, parallel-group randomised controlled trial with two study arms: (1) calorie intake in meal-1 and (2) no calorie intake in meal-1. Participants and healthy controls are individually randomised to either one of the two arms, both delivered at the eating disorder clinic of the Ege University Hospital, Faculty of Medicine.

The primary outcome measure is brain patterns observed with functional MRI, and secondary outcomes include endocrine markers in blood, cardiovascular responses, self-reported symptom severity and subsequent food consumption.

The study is planned following the Standard Protocol Items: Recommendations for Interventional Trials^(53,54)^ and will be analysed and reported following the recommendations in Consolidated Standards of Reporting Trials^(55)^, with special care taken to meet extended recommendations for both trials with patient-reported outcomes^(56)^ and non-pharmacological trials^(57)^.

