### Randomisation

When an eligible participant has been recruited and consented, they will be scheduled for randomisation at a later timepoint. AN participants will be individually randomised to one of the two study arms with a 1:1 allocation ratio by a computer-generated allocation sequence using permuted blocks. The block sizes will vary randomly between two and four.

Randomisation lists will have been pre-prepared by a separate researcher who is not involved in participant recruitment. Sealed envelopes will contain the study ID for each participant and the meal assigned to that individual (caloric or non-caloric). When a participant is ready to enter the study, a researcher will draw an envelope and prepare the assigned meal for that participant in the evening for consumption the next morning.

Participants with AN will be admitted to the clinic’s open inpatient unit on the evening prior to study participation to ensure a 12-h overnight fast. On the following day, they will receive the specified interventions and undergo the outlined assessments. Once an AN participant has been randomised and completed the study, a matched healthy control participant will be recruited. Recruitment of healthy control participants will be conducted by study personnel who are masked to the randomisation outcomes of the corresponding AN participant. This approach ensures that the allocation of both AN and healthy control participants remains concealed from recruiting researchers and those conducting assessments. Healthy control participants will undergo the same eligibility assessments as AN participants, be assigned their own study ID and share the same allocation as their corresponding AN participant. However, unlike AN participants, healthy control participants will not be admitted overnight.

Codes will be used to increase information confidentiality and participant anonymity, and participant allocation will be performed based on these codes. Randomisation will continue until *n* 36 AN patients and *n* 36 healthy controls have completed the study as per-protocol participants.

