### Statistical methods

#### Analysis plan

Analysis will be conducted once data collection is complete. No interim analyses will be performed. Initially, the quality and completeness of the data will be assessed. If available, missing values will be entered using information from the individual’s original data file. The dataset will be examined for outliers and inconsistencies. For categorical variables, any responses outside the defined categories will be coded as missing. For continuous variables, values outside the acceptable ranges will also be coded as missing. Missing data will not be imputed.

The analyses will be carried out by the investigators and a biostatistician using the latest version of SPSS Statistics (IBM Corp.), R (R-core team) or equivalent statistical software. For the analysis of functional MRI data, additional software tools described below will be used. Data analysts will be blinded to the participants’ allocation. Significance testing will be two-tailed, and statistical uncertainties will be reported as 95 % confidence intervals. All tests will be conducted with a significance level of 0·05.

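### The 70% power belongs to the AN versus healthy comparison; no power is stated for the meal-by-diagnosis contrast that the primary hypothesis tests, and at 0.6 SD that contrast has roughly 24% to 69%

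*Protocol article*

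**What the plan says.** All references are to the protocol article.

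- **Sample size calculation.** The section opens "A two-tailed power calculation for 70 % power and" a 0.05 level, for a t test "with linear regression (two independent groups") and "an effect size of d = 0·6, based on results from similar neuroimaging studies", "determining that thirty-four participants per group (AN/healthy) would be sufficient". Recruitment is set at 36 per group to allow for dropout. No other contrast is sized.
- **Introduction, objectives paragraph.** The primary objective is to separate the neural responses to the caloric and non-caloric meals and to establish "how this differs between newly diagnosed adolescents with AN and matched healthy controls". The hypothesis that follows is that calorie-dependent change in network activity is not the same in the two diagnosis groups.
- **Randomisation.** Patients are allocated 1:1 to the two meals. Controls "share the same allocation as their corresponding AN participant".
- **Design.** "Participants and healthy controls are individually randomised to either one of the two arms".
- **MRI, Primary analysis and Analysis plan.** Resting-state scans are taken at T0 and T2, and change across the meal is evaluated. The regression includes meal type and AN status, with random effects for participant and matched pair. False discovery rate control is applied to the regression betas. "All tests will be conducted with a significance level of 0·05".

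**The concern.** The contrast that was sized is not the one the trial asks about. AN versus healthy is not randomised and takes no account of the meal. The stated hypothesis is a difference of differences: the caloric-minus-non-caloric effect in patients less the same effect in controls. With 36 patients and 36 controls each split 1:1, it rests on four cells of 18. At equal SD and independent observations, its variance is four times that of a comparison of two groups of 36.

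What is at stake is how the result will be understood. A reader who sees 70% power beside that hypothesis will apply the 70% to it, and may then take a non-significant interaction, or a non-significant calorie effect within AN, as better evidence of no effect than the design can supply.

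**Working it through.** **Inputs from the article.** Two-sided alpha 0.05; target power 70%; d = 0.6 (SD set to 1); 34 per diagnosis group, 36 recruited; 1:1 meal split in patients; controls take the matched patient's meal. This gives four cells of 18.

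**Inputs assumed.** The article gives no T0-T2 correlation (r), no correlation within matched pairs (rho), no size for the interaction, and does not say whether d is on the post-meal or the change scale. I take 0.6 SD for the interaction on the post-meal scale, r = 0.5 to 0.7, and rho = 0.3 to 0.5 (remaining after T0 adjustment). All powers are for one test, from the noncentral t distribution.

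**1. The printed figure.** SE = sqrt(2/n), df = 2n − 2.
- n = 34: noncentrality 0.6/sqrt(2/34) = 2.47, power 68.4%.
- n = 35: power 69.7%.
- n = 36: noncentrality 0.6/sqrt(2/36) = 2.55, power 70.9%.

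The normal approximation asks for 35 per group. The printed 34 is therefore within two participants and two power points, and it reproduces only with everyone of the same diagnosis in one group.

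**2. Meal-by-AN-status interaction, unadjusted, independent pairs.** SE = sqrt(4/18) = 0.471, df = 4 × 18 − 4 = 68, noncentrality 0.6/0.471 = 1.27.
- Power 24.1%.
- Interaction detectable with 70% power: 1.19 SD.

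**3. The same contrast, using the planned baseline scan and the matching.** T0 adjustment multiplies the SD by sqrt(1 − r²). Since partners share a meal, the interaction can be tested by comparing pair differences between meals, 18 v 18: SE = sqrt(1 − r²) × sqrt(2(1 − rho)) × sqrt(2/18), df = 34.

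| r (T0-T2) | rho (pair) | SE | Power at 0.6 SD | Detectable at 70% |
|---|---|---|---|---|
| 0 | 0.3 | 0.394 | 32% | 1.01 SD |
| 0 | 0.5 | 0.333 | 42% | 0.85 SD |
| 0.5 | 0.3 | 0.342 | 40% | 0.87 SD |
| 0.5 | 0.5 | 0.289 | 52% | 0.74 SD |
| 0.7 | 0.3 | 0.282 | 54% | 0.72 SD |
| 0.7 | 0.5 | 0.238 | 69% | 0.61 SD |

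T0 adjustment alone, with independent pairs and 68 df, gives about 30% (r = 0.5) and 42% (r = 0.7), with detectable interactions of 1.03 and 0.85 SD.

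**4. Calories versus none within AN.** SE = sqrt(2/18) = 0.333, df = 34, noncentrality 1.80.
- Unadjusted: power 41.7%, detectable effect 0.85 SD.
- With T0 adjustment: 52% (r = 0.5) and 69% (r = 0.7), detectable effects 0.74 and 0.61 SD.

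**5. Two boundary cases.**
- An interaction of 1.2 SD (calories move patients by −0.6 and controls by +0.6), unadjusted: noncentrality 1.2/0.471 = 2.55, df 68, power 71%.
- The meal effect pooled over diagnosis, 36 v 36, independent pairs: 71%, by the same arithmetic as step 1. Positive pair correlation would lower this one, because partners receive the same meal.

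**The case against.** The strongest reply is that 24% is the low end and not a property of the planned design. The plan scans twice, studies change, and models the matched pairs; using both features gives about 40% to 69%. This stands, and it is why the result is given as a range. It depends on d being a post-meal effect. If d already refers to change, the baseline gain in step 3 is not available and only the matching helps: 24% unadjusted with independent pairs, up to 42% at rho = 0.5.

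Second, the article gives no size for the interaction. It reports opposite hypothalamic metabolite responses to feeding in patients and lean individuals, so a crossover is conceivable, and a crossover of 1.2 SD would have 71% power. That also stands as a scenario. It concerns a different measure, however, and the article does not use it to justify the sample size.

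Third, the regression description lists meal and AN status without naming their interaction, so the primary contrast is inferred from the objective and hypothesis. This is fair, but those statements are plain. If calories within AN were primary instead, power would still be about 42% unadjusted.

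Stronger readings that the documents do not support:
- *The sample size arithmetic is wrong.* It reproduces closely; the fault is the contrast chosen.
- *The 70% holds only for AN versus healthy.* The meal effect pooled over diagnosis also has about 71% if pairs are independent.
- *Giving controls their partner's meal weakens the interaction test.* Positive pair correlation raises its power. The conflict between the Design and Randomisation sections is a separate defect.
- *The investigators will report a null as no difference.* Nothing says so, and the Analysis plan already commits to 95% confidence intervals. The risk lies in how the 70% will be read.

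**Conclusion.** The concern holds as a mismatch between the stated power and the stated question. The 70% at d = 0.6 describes AN versus healthy on a single test. For the meal-by-AN-status contrast, a 0.6 SD effect has about 24% power unadjusted with independent pairs, and about 40% to 69% under the combined correlations assumed here. It does not reach 70% within that range. The unadjusted interaction detectable with 70% power is about 1.19 SD, roughly twice the effect used for sizing. Calories within AN has about 42%, or 52% to 69% with T0 adjustment.

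These figures rest on 18 per cell, a 0.6 SD effect on the post-meal scale, and correlations that the article does not give. They are for one test. False discovery rate control over several connections and graph metrics would be expected to lower them, by an amount that cannot be fixed without the number of tests.

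**What to change.** Keep 36 + 36 and make these changes before the data are analysed:

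1. In Sample size calculation, state that the 70% at d = 0.6 refers to AN versus healthy and to a single test before false discovery rate control.
2. Add power and detectable effects for the meal-by-AN-status interaction and for calories versus none within AN. Give them as ranges, with the assumptions beside them: the scale of d, the T0-T2 correlation and the pair correlation. The figures above can serve until the trial team has its own values for the correlations.
3. State that a non-significant interaction will be interpreted from its 95% confidence interval and not as evidence of no difference. The intervals are already planned, so this adds only the rule for reading them.
4. Separately, reconcile Design with Randomisation. Under the latter, patients are randomised and each control takes the matched patient's allocation, so the randomised units are 36 pairs and not 72 individuals.

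The cost is a less favourable set of stated figures and a few sentences of text. No additional patients and no change to trial conduct are needed.

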## Discussion

The NAMA trial will be the first randomised controlled trial in AN that distinguishes between psychological and metabolic neural networks in the brain. The trial is designed to uncover how these networks are associated with food intake and explain how their integration affects food intake and other hallmark symptoms of AN. Recruitment of patients and healthy controls, intervention delivery and data collection started at the beginning of 2025, and the last follow-up that will be presented in the primary manuscript is expected to be completed in 2026. The present article presents the overall methods of the experiment and the main analyses that are planned to be performed. It was written to prepare for future analyses and to increase the transparency of scientific conduct, as well as to enable others to comment on our proposed strategy. In this way, the results will be as robust and transparent as possible.

AN is a severe mental disorder for which available treatments are far from satisfactory^(67)^. This is partially due to the scarcity of clinically integrated mechanistic experiments. It is, for example, unclear how psychological factors affect the development of AN^(15,23,24)^, and emerging evidence suggests that psychological factors interact with metabolism to precipitate AN^(25–27)^. AN is associated with a perturbed response to metabolic signals of food intake^(25,39)^, and this is associated with altered brain activity^(40,42)^. No previous report has clarified how this perturbed metabo–psychological integration contributes to AN development and maintenance^(52)^.

The design of the NAMA trial makes it possible for the first time to reveal how the integration of metabolic and psychological factors drives AN pathology by performing a two-meal behavioural test with multiple assessments of brain network activity, physiological parameters and psychometric data. A single study on AN rarely collects neuroimaging data, blood samples, physiological parameters and psychometric data. Masking participants to oral intake of food with and without calories has, to our knowledge, not been performed by anyone in the past. This is expected to activate metabolic responses in a way that is closer to the natural biological reactions to food intake than feeding through a nasogastric tube. The NAMA trial is also original in focusing on treatment-naïve adolescents with AN. Treatment-naïve adolescents with AN are an understudied group that is expected to shed much-needed light on the mechanisms of AN, as adolescence is the period in which disease onset peaks^(4–6)^. In addition, the inclusion of healthy controls will enable researchers to dissect the distinct mechanisms in patients in a way that is disease specific. Unlike most other AN studies aimed to reveal disease mechanisms, using the randomised controlled trial method enables masking, which reduces many common biases^(55)^. The randomised controlled trial method is also considered the most rigorous ‘gold-standard’ way of testing experimental medical interventions^(68)^. With such a broad approach, the NAMA trial will make it possible to uncover the mechanisms that drive AN in ways that were previously impossible.

Through the integration of multifaceted data from patients and healthy controls, the NAMA trial may thus change the way we understand the metabolic effects of calorie intake in health and disease and in particular what distinguishes the physiology of AN patients from that of healthy individuals. This may open the door to new therapeutic alternatives and change how patients with AN are seen and treated. Indeed, the view of AN as resulting from psychological processes that induce dieting does not account for the amount of recent data that suggest that AN develops out of an interaction between psychological and metabolic factors^(28,69)^, and this may have delayed targeted drug development for this disorder.

The present study should be assessed with some limitations in mind. First, the analysis plan has purposefully been formulated somewhat loosely, and in so doing, it is not possible to take full advantage of one of the main reasons for methodological pre-specification: to prevent selective outcome reporting. The field of neuroimaging in general and neuroimaging of AN in particular evolves quickly, and it is expected that in 2 years, there will be both new methodological approaches to analysis, particularly new machine learning algorithms, and new neuroimaging studies of AN that need to be considered will have been published. Additionally, we are performing parallel *in vitro* and rodent experiments that will inform the region-of-interest selection and analysis. To enable such translational synergistic effects, it was considered necessary to formulate the analysis plan in this way. All the other purposes of pre-specifying a research strategy are still fulfilled^(70)^, and results will be assessed based on biological feasibility. Second, it is anticipated that some participants with AN will be unwilling to consume the full amount of mixture prepared in meal-1 or to consume meal-2. This may result in reduced contrast between study arms; however, it is not expected to bias the results with type-1 errors. The mixtures were designed to be small enough for ease of consumption yet large enough to produce a metabolic effect and to recruit newly diagnosed patients with AN, which is expected to facilitate the intake, as these individuals are unlikely to have advanced disorders. Third, it is unclear to what extent the masking of participants will be successful, as the approach is still somewhat novel. Even if some unmasking occurs, the study may be able to detect important differences between participants with AN and healthy controls, although the individual effects of psychological and physiological processes will not be fully disentangled. Apart from the participants, all individuals involved in the study are expected to be successfully masked. Finally, the trial evaluates neuroimaging, physiological, subjective and behavioural outcomes with a short follow-up time. Given the limited intervention involved, there is no intention to treat participants, and therefore, no clinical outcomes or hard endpoints are included.

### Conclusion

The NAMA trial will distinguish psychological and metabolic neural networks in the brain, uncover how these are associated with food intake and explain how their integration affects food intake and other hallmark symptoms of AN. This study will thereby reveal neurobiological mechanisms driving AN.

## Table 1 Long description

A table summarizing trial registration data for a study on anorexia nervosa. The table has 16 rows and 2 columns. The columns are labeled 'Data category' and 'Information'. Row 1: Primary registry and trial identifying number, ClinicalTrials.gov NCT06814002. Row 2: Date of registration in the primary registry, 2025-02-06. Row 3: Primary sponsor, Umeå University, Ege University. Row 4: Contact for public and scientific queries, [name]. Row 5: Public title, NAMA trial. Row 6: Scientific title, Networks integrating anxiety and metabolism in anorexia nervosa trial. Row 7: Countries of recruitment, Turkey. Row 8: Health condition studied, Anorexia nervosa. Row 9: Interventions, Meal with 400 kcal and meal without calories. Row 10: Key inclusion and exclusion criteria, Inclusion criteria: female sex, 13-18 years of age, patient at the eating disorder clinic, AN DSM-5 diagnosis, treatment naïve. Healthy controls are accepted (eating disorder in the present or past is an exclusion criterion for them). Exclusion criteria: chronic medical conditions, medications that affect hormone levels or eating behaviours, severe psychiatric disorders other than AN, drug abuse, pregnancy, high risk of refeeding syndrome, allergies to provided meal content, cognitive impairment, contraindications for MRI, fasting blood glucose above 6.0 mmol/l on the morning of the study. Row 11: Study type, Interventional. Row 12: Allocation, randomised. Row 13: Primary purpose, mechanistic research. Row 14: Date of first enrolment, 2025-02-15. Row 15: Target sample size, 72. Row 16: Recruitment status, Recruiting. Row 17: Primary outcome, MRI. Row 18: Key secondary outcomes, Food consumption, psychometric scales, blood samples, blood pressure, pulse.

Navigate back to Table 1.

